Focus group B	To receive feedback on a draft intervention	Three focus groups (*n* = 8 in each group) will be run using professionals, people with dementia, and their study partners	Information from the preceding stages will be integrated to inform a draft intervention, which which will be presented to participants for comment and feedback	These will be the same three sites that participated in focus group A; however, the participants may differ between the two focus groups	As with focus group A, discussions will be transcribed and analysed using content analysis
Field Trial of draft intervention	To trial a ‘sensory support’ intervention for people with dementia and sensory impairment	Eight participant dyads (people with dementia and sensory impairment and their study partners) in each of three sites	A 12-week ‘sensory support’ intervention involving correction of hearing/vision impairments, communication training, ‘sensory proofing’ the home environment, and signposting to relevant services. Baseline and follow-up data will be collected along with process measures and reflective diaries	Three sites will recruit a total of 24 participant dyads: Manchester, Nicosia, and Bordeaux	Data from the diaries and verbatim data from the interviews will be analysed using a summative content analysis. Quantitative parametric data will be analysed using two-tailed *t* tests, with 95% CIs. Effect sizes using the Hedges’ g formula (similar to Cohen’s d), appropriate for small sample sizes will be calculated. Due to the small sample, only a large *p* value, 0.2, will be an indication of effect. The score distributions will be examined for degree of variability and ceiling and floor effects. Participants’ subjective report of the overall helpfulness of the intervention will give an initial impression of efficacy. An initial impression of treatment efficacy will be obtained by examining before and after-intervention measures of a variety of rating scales of dementia-related outcomes

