### Step 4: Field testing the draft intervention

The final step in the programme will be to field test the draft sensory support intervention with a participant population representative of the group who will participate in the subsequent RCT of the intervention, should the results of the field test be positive.

*Objective:* The field study will have three objectives: (1) to undertake a process evaluation of the components and implementation of the intervention, including reach and fidelity issues, acceptability and tolerability of the intervention for participants as well as the contextual issues; (2) to examine the operational aspects of a future trial design, including recruitment and retention and training methods and materials; and (3) to explore the feasibility and face validity of potential outcome measures for the future trial. As the field trial comprises a complex, multi-faceted study, it is described elsewhere in detail ([name], et al. Improving hearing and vision in dementia: protocol for a field trial of a new intervention, in submission). The current description is comprised of a brief overview of the field trial in the context in which it has been developed.

*Method:* This will be an open-label feasibility study in people with dementia and sensory impairments and their caregivers in each of three clinical sites. There will be no control group. Participants, researchers and sensory support workers will not be masked to intervention assignment and all participants and their caregivers will receive either the full draft intervention package or certain components of the package decided a priori. Whether or not the individual receives the full intervention or a reduced version will depend on their availability, interest and need for support in certain areas.

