*Study procedures:* The procedures are summarised in Fig. 2. Briefly, the study will take place over a period of three months with a series of interventions offered by professionals (opticians and audiologists), sensory support workers (SSW), and researchers undertaking the outcome assessments. Following recruitment, participants will be required to provide informed consent to participate. In order to overcome potential issues with consent presented by functional and sensory impairments, the researcher will be able to fill in the consent form on behalf of the individual and countersign to confirm that verbal consent has been provided. Following the signing of consent, potential participants will be screened for suitability to be included in the study. Screening will entail brief checks of hearing (using the SIEMENS HearCheck), vision (using the PEEK acuity smartphone application) and cognition (using the MoCA). For those who pass screening, a clinical assessment of vision and hearing status will be arranged. Vision status will include refraction, visual acuity, fields and contrast sensitivity. Hearing status will include otoscopy, tympanometry and pure tone audiometry. If surgical or invasive corrections are required (e.g. for cataracts or macular degeneration), the participant will be withdrawn from the study. If non-surgical sensory corrections or improvements can be provided with devices (hearing aids and/or lenses), these devices will be offered and fitted. Fitting and uptake of the new devices will be supported by the SSW who will visit the participant at home. Once impairments have been optimally corrected, a home-based assessment of vision and hearing functional ability will be undertaken in order to assess the specific support care needs of the participant and their caregiver. Based on the needs identified, a sensory support package will be offered to the dyad, based on the COM-B framework outlined above [23]. The specific components (e.g. content of each module) and manner of implementation (e.g. frequency and duration of support visits) will be determined from the intelligence gathered in steps 1 to 3 of the research programme. The final protocol outlining the study procedures and the draft intervention to be field tested will be prepared at the end of step 3. A researcher will undertake a series of process evaluations at each step of the protocol in order to ascertain such outcomes as feasibility, tolerability, acceptability and fidelity and reach of the intervention. The evaluations will involve participant diary keeping, direct researcher observations of visits, participant satisfaction scales, and SSW and researcher feedback. At the end of the intervention, each participant:caregiver dyad will participate in a 1–2 h semi-structured interview with the researcher to give feedback on the intervention components and implementation. A similar evaluation will be undertaken to ascertain successful aspects of trial procedures and outcome measures used. The outcomes to be explored will include measures of quality of life, mood, well-being, cognitive and functional ability, caregiver indices (e.g. burden, stress, well-being, and mood) and health economic measures.

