
**Fig. 2 Fig2:**
[figure not shown]
Flowchart of the components of the field test

*Analyses:* Demographic and baseline data will be fully described, and all outcome data will be analysed and reported. The quantitative evaluation will be a description of the rates of recruitment and retention over the period of the study, the tolerability and utility of the assessment procedures, as well as a description of the participant reaction to the intervention components and the frequency and duration of the therapy sessions as reflected by the in-house post-session rating scale. Fidelity of the intervention, as per Lichtstein et al. [46], will be analysed for content, as derived from the SSW, researcher and participant outcome data. The qualitative data from the semi-structured interviews will follow the same methods as described above for steps 2 and 3.

The outcome of the Field Trial will determine whether we will proceed to a full scale efficacy trial. Reasons for not proceeding to a full trial will be determined on the basis of the detailed process analysis of the draft intervention components and implementation, as well as the operations of the trial procedures being tested in the Field Trial. These will include measures of participant acceptability, tolerability, and feasibility of the intervention; the practical aspects of the logistics circuit regarding the supply and delivery of the corrective devices (glasses and hearing aids); the meaningfulness and feasibility of the outcome measures; and other key aspects informing a full scale trial. The specifics of these interventions are outlined in a protocol of the SENSE-Cog Field Trial ([name], et al. Improving hearing and vision in dementia: protocol for a field trial of a new intervention, in submission).

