### Dissemination

The dissemination plan for the programme will have two key objectives: (1) a set of internal reports of the outcomes of each activity of the programme in order to inform the study team of the next steps in the overall intervention development and (2) manuscripts and reports with outcomes of selected activities for external communication. These latter will comprise lay communications for the SENSE-Cog website and for public newsletters, as well as scientific manuscripts for publication in open-access peer reviewed professional journals. Specifically, the scientific outputs will include the systematic literature reviews, a support care needs’ analysis from the patient and significant other perspective, a support care needs’ analysis from the professionals’ perspective, a description of the final field tested intervention package, a process analysis of the field trial with a report of preliminary efficacy findings and the protocol of the development programme. The lay reports, led by the PPV groups, will be made available in each of the SENSE-Cog partner sites through local charity newsletters, websites and bulletins. The wider SENSE-Cog programme has a comprehensive dissemination strategy which will be utilised with regard to the output of the current work. This includes outputs posted on social media sites.

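### Table 2 reads efficacy from single-arm, unmasked before/after change and helpfulness ratings, which the design cannot support and the sample size paragraph rules out

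*Protocol article*

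**What the plan says.** **Table 2, field trial row, data analysis column.** Efficacy is read from two sources. One is within-person change: "An initial impression of treatment efficacy will be obtained by examining before and after-intervention measures". The other is opinion: participants' "subjective report of the overall helpfulness of the intervention will give an initial impression of efficacy". The same cell plans two-tailed t tests with 95% confidence intervals and Hedges' g, and says that, because the sample is small, a p value of 0.2 will be read as indicating an effect.

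**Dissemination.** The scientific outputs include "a process analysis of the field trial with a report of preliminary efficacy findings".

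**Step 4, Objective and Method.** The three objectives are a process evaluation, the operational aspects of a future trial, and the feasibility and face validity of candidate outcome measures. On design: "There will be no control group", and "Participants, researchers and sensory support workers will not be masked to intervention assignment". Under Study procedures, the same unmasked group is described as "researchers undertaking the outcome assessments".

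**Step 4, Sample size.** Twenty-four dyads, 8 at each of three sites. There is no power calculation, on the ground that inferential efficacy analyses are not planned.

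**Progression.** Step 4 opens by making the later trial conditional: "should the results of the field test be positive". The Analyses paragraph says: "Reasons for not proceeding to a full trial will be determined on the basis of the detailed process analysis".

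**The concern.** With one arm, the mean before/after change is the sum of any treatment effect, expectancy, regression to the mean and 12 weeks of a progressive disease. No part of the data separates these. Participants and assessors both know that the intervention was given, and the intervention is a supportive home programme, so ratings may improve without any sensory benefit. Disease progression may pull the other way, so even the direction of the net bias is unknown.

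Helpfulness ratings answer a different question. They show whether participants liked the programme and found it useful, which is acceptability.

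The article also disagrees with itself. One place plans tests with a threshold for effect, and another says that no such inference will be made. If Table 2 and the Dissemination section are followed, the field trial paper will carry an efficacy statement that the design cannot support. Planners of the definitive trial could then take it as a guide.

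**Working it through.** **1. The passages side by side**

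| Question | Table 2 and Dissemination | Step 4 |
|---|---|---|
| Is efficacy a purpose? | Yes: two impressions of efficacy, then a published report | Not among the three objectives |
| Is there inference? | t tests, with p = 0.2 indicating effect | No inferential efficacy analyses planned |
| Is there a comparator or masking? | Not mentioned | Neither |
| What are the scores for? | Evidence of effect; also variability and floor/ceiling | Feasibility and face validity of measures |

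The two columns cannot both be followed. The Discussion does not name the lack of a control group or of masking as a limit on the efficacy reading.

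**2. The plan's own figure**

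8 dyads × 3 sites = 24, which agrees with the text. No effect size, SD or power is stated, so nothing else can be reproduced.

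**3. What the p = 0.2 rule would flag (illustration)**

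Inputs from the article: n = 24, two-tailed t test, p = 0.2. Assumptions: a paired test on the change scores and 24 complete pairs.

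- Critical value: t(0.90; 23 df) = 1.319.
- Smallest mean change flagged: 1.319 / √24 = 1.319 / 4.899 = 0.27 SD of the change scores.
- With no treatment effect and no drift, a scale is flagged 20% of the time, 10% in the favourable direction.

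Now let the true treatment effect be zero and let scores drift favourably by d SD of change, for non-specific reasons. The chance of a favourable flag is P(T > 1.319), where T is noncentral t with 23 df and noncentrality d√24.

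| Assumed drift d | d√24 | Chance of a favourable flag |
|---|---|---|
| 0 | 0 | 10% |
| 0.1 | 0.49 | 21% |
| 0.2 | 0.98 | 37% |
| 0.3 | 1.47 | 56% |
| 0.4 | 1.96 | 74% |

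With only 18 complete pairs, the chance at d = 0.3 is 48%.

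**4. The other direction**

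Suppose a true benefit of 0.4 SD is offset by a decline of 0.2 SD. The net shift is 0.4 − 0.2 = 0.2 SD, and the chance of a favourable flag falls from 74% to 37%. The rule can therefore hide a real benefit as easily as it can suggest a false one.

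None of these shifts is given in the documents. The table shows how the rule behaves; it does not predict the result.

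**The case against.** **The wording is hedged.** The text speaks of an initial impression and of preliminary findings, and it leaves efficacy to a later full-scale trial. That is fair, and it limits the seriousness. But the hedge concerns precision, and the difficulty is confounding: a single-arm study of any size would have it.

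**A single-arm, open-label design is normal for feasibility work.** Agreed. The design suits the Step 4 objectives, and no control group is asked for.

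**Looking at change serves a stated purpose.** The Primary specific objectives section asks Step 4 to identify suitable outcome measures, including for impact on well-being, quality of life and caregiver burden. This stands as a reason to collect and report change scores. It is not a reason to call them efficacy or to apply a threshold for effect.

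**The article is an overview.** It refers to a separate field trial protocol, where caveats and progression criteria may well appear, so their absence here is not held against it. What counts is what the article affirmatively states.

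**The go decision.** A reader might infer that favourable before/after change would trigger the definitive trial, since the Overall aims section and the opening of Step 4 make it depend on positive results without defining the term. The documents do not support that. The Analyses paragraph of Step 4 rests reasons for not proceeding on process: acceptability, tolerability, feasibility, device logistics and the performance of the outcome measures. Its list ends with other, unspecified key aspects, so change scores are not expressly excluded, but nothing makes them a formal criterion.

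**Conclusion.** The point holds as one of analysis and interpretation. Table 2 and the Dissemination section commit to an efficacy reading that an uncontrolled, unmasked study cannot give, that is not among the Step 4 objectives, and that conflicts with the sample size paragraph. Helpfulness ratings are mislabelled as efficacy. These conclusions rest on the text and the design alone.

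The 37% to 56% chance of a favourable flag is illustrative only. It assumes 24 complete pairs, a paired t test, and a favourable drift of 0.2 to 0.3 SD of change, none of which the documents supply. It should not be read as an expected false-positive rate, because disease decline could push the other way.

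The plan should be corrected before the field trial is analysed. The design and the sample size are not in question.

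**What to change.** - **Table 2, field trial row.** Delete the rule that p = 0.2 indicates an effect, and delete both sentences that derive an impression of efficacy. Report helpfulness ratings as acceptability. Report change scores descriptively (mean and SD of change with 95% CI, completeness, floor and ceiling effects) to assess the candidate outcome measures. State that change cannot be attributed to the intervention. The row then agrees with the Step 4 sample size paragraph.
- **Dissemination.** Replace the promised preliminary efficacy findings with *performance of candidate outcome measures*.
- **Clarification only.** In the Overall aims section and at the opening of Step 4, say that a positive outcome means meeting the process criteria in the Analyses paragraph of Step 4.

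These are changes of wording. No new data, sample size or design follows from them. The cost is that the field trial paper gives up an efficacy statement.

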### Participants

Throughout the programme, we will engage with four groups of participants in each of the three participating centres. The specific inclusion/exclusion criteria for each of these groups will be outlined in more detail in the description of each of the steps. All participants will be required to have the capacity to consent in order to participate. Capacity checks will be made in accordance with the UK’s Mental Capacity Act 2005 [24]. The four groups of participants are as follows:i.People ≥ 60 years of age with mild to moderate dementia (due to Alzheimer disease (AD), vascular dementia or mixed AD/vascular dementia) and vision or hearing impairments. Individuals with severe dementia will be excluded from the study on the grounds that the field trial, which is the end point study in the development process, involves completing several outcome measures and engaging with a complex, multifaceted intervention, which may potentially place too much burden on individuals with more severe dementia.ii.Study partners of the affected people, who will likely be spouses or unpaid caregivers (significant others).iii.Expert professionals representing different disciplines pertaining to the programme’s goals, including geriatric psychiatry, audiology, vision science, ophthalmology, social gerontology, optometry, occupational therapy, social work, health psychology and statistics.iv.Representatives of PPV who are part of the team’s Research User Group (RUG).

### Settings

The ERG will take place in Athens, an EU city with easy access for the experts and in close proximity to the SENSE-Cog consortium members from Greece who can support the operations of the group. The PPV consultations will take place in each of three clinical sites: Manchester, Nice and Nicosia. The clinical sub-studies (Needs Survey, Focus Groups and Field Test) will take place in each of three sites with the following sponsors: the University of Manchester, European University Cyprus, and the University of Bordeaux.

### Recruitment

Recruitment of expert participants will be informed by the literature and through professional contacts of members of the wider SENSE-Cog team, which is a multi-disciplinary consortium of professionals addressing all aspects of the study programme. Recruitment of the PPV members will take place in each of the relevant sites by placing notices in the newsletters and websites of local charities, support groups and existing PPV networks. Participants who are people with dementia and their caregivers or significant others will be recruited from memory clinics in Manchester, Bordeaux and Nicosia through direct contact with their treating clinician.

### Study design, methods and analyses for each step in the programme

In order to achieve our aims, we have divided the development programme into four distinct steps: (1) defining the gap in care and scoping the existing evidence of the impact of sensory deficits in dementia, (2) developing a prototype intervention, (3) refining the prototype into a draft intervention, and (4) field testing the draft intervention.

### Step 1: Defining the gap in care and scoping the existing evidence of the impact of sensory deficits in dementia

#### Systematic and rapid literature review

*Objective:* To assess the impact of treating hearing and vision impairment on (1) cognition, (2) rate of decline, (3) psychiatric symptoms, (4) hearing/vision-related quality of life, (5) health-related quality of life, and (6) caregiver burden for people with dementia.

*Method:* Electronic databases will be systematically searched using the key terms and their synonyms: dementia AND (hearing impairment/deaf OR sight/vision impairment) AND, (intervention OR rehabilitation OR management OR treatment OR outcome). Databases searched were Google Scholar, MEDLINE, Cochrane Central Register of Controlled Trials, EMBASE, PsychINFO, CINAHL, AgeInfo, Web of Science, Scopus, ComDisDome, Open Grey, ClinicalTrials.gov and the WHO international clinical trials registry. The database searches will be supplemented by searching through bibliographies of papers that match the eligibility criteria and via consultation with a network of health professional experts to identify additional grey literature that has not been found via the database search.

*Analysis*: Screening of both titles and abstracts will be done by two independent reviewers. All disagreements will be resolved by discussion or consultation with a third reviewer if necessary. Risk of bias assessment and data analysis will be completed and reported in a narrative review.

#### Gaps identified from professionals’ expertise and experience

*Objective:* To ascertain the views from professionals within the domains of dementia, hearing and vision impairment regarding the ‘gaps and solutions’ in the support care needs of people with concurrent problems.

*Method*: Face-to-face guided discussion and written survey in the context of an ERG, held over 2 days in Athens, Greece. Each participant will be asked to present their pre-prepared answers to the following questions prior to the meeting: ‘What are the key gaps in knowledge in the field from your professional perspective?’; ‘What problems might you encounter if the person has concurrent hearing/vision/cognitive problems in a clinical setting?’; and ‘What solutions might you offer to the problems that might arise?’.

Directions will be given to the experts advising them that the focus will be on their direct clinical experience and research expertise in the field.

*Participants*: Expert professionals (*n* = 20), identified through the rapid literature review and personal contacts of the members of the SENSE-Cog consortium, will be invited to an ERG. The experts represent the disciplines described above and will come from member countries of the SENSE-Cog consortium (England, France, Germany, Cyprus, Greece) in addition to Canada and Wales.

*Analysis*: We will use qualitative thematic analysis of responses to describe the range and content of the expert opinions.

